### Physiotherapy and rehabilitation

A back splint will be used for 3 to 4 days. The patients will perform edema prophylactic exercises during the time of immobilization. All patients will follow a standard rehabilitation program supervised by a physiotherapist. This includes active flexion and passive extension of the elbow the first 2 weeks, active flexion and extension without any weight bearing from 3 to 6 weeks, and weight bearing after 6 weeks. Full weight-bearing exercises are allowed after 3 months.

### Outcome measures

#### Primary functional outcome

The Oxford Elbow Score (OES) will be used to assess the primary outcome at 2 years.

The OES is a 12-item, patient-administrated questionnaire that measures the quality of life in patients with an elbow disorder. There are three unidimensional domains: elbow function, pain, and social-psychological status [5, 13]. Each question is answered on a five-point scale with each question contributing equally to the total score. Thus, the total score ranges from 12 to 60, with 60 being the worst. For ease of presentation the score is converted to a scale from 0 to 48 with 48 being the best. The outcome can be interpreted based on a 48-point scale: 0–19, poor; 20–29, fair; 30–39, good; and 40–48, excellent [6]. The Danish version, which will be used in this study, has been translated and culturally adapted according to the guidelines by Guillemin, Bombardier, and Beaton [6, 21].

The minimal clinically important differences (MCID) for the total score of OES has not been defined, but Dawson et al. reported the MCID for each of the three domains, pain, function, and social-psychological. The MCID for the three domains was 19, 9, and 18, respectively [5]. Accordingly, we estimated the MCID for the total score to be 15.

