### Statistics

#### Sample size calculation OES

Oxford elbow score (OES) will be used to measure the primary outcome.

Sample size calculation was performed with a standard deviation (SD) of 16, a MCID of 15, a significance level at 0.005, and power of 0.80, resulting in 18 participants in each group (44 participants in all with allowance for 18% drop-out).

The estimation of SD = 16 is extrapolated from a study on 24 patients with distal humeral fractures treated with EHA [1]. There is no MCID defined for the total score of OES, but Dawson et al. have reported the MCID for each of the three domains—pain, function, and social-psychological—for a group of patients with different pathologies including TEA for osteoarthritis and rheumatoid arthritis. MCID for the three domains is 19, 9, and 18, respectively [5]. Accordingly, we chose the MCID to be 15.

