#### Hypotheses

We hypothesize that at 2 years, EHA provides a superior OES compared with ORIF by at least a difference of 15.

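### The OES target difference of 15 is taken, without conversion, from domain MCIDs that cannot be in points of the 0–48 total score on which the primary outcome is defined

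*Protocol article*

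**What the plan says.** Under Primary functional outcome, the protocol article states: "The Oxford Elbow Score (OES) will be used to assess the primary outcome at 2 years". It describes the instrument: "The OES is a 12-item, patient-administrated questionnaire", with three domains (function, pain, social-psychological). On scoring it says "Each question is answered on a five-point scale with each question contributing equally to the total score". The raw total runs from 12 to 60, and "the score is converted to a scale from 0 to 48 with 48 being the best". The same section grades results on that 48-point scale: poor 0–19, fair 20–29, good 30–39, excellent 40–48.

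It notes that no MCID exists for the total score, cites one for each domain, and concludes: "Accordingly, we estimated the MCID for the total score to be 15".

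Sample size calculation OES repeats the derivation ("MCID for the three domains is 19, 9, and 18, respectively", for pain, function and social-psychological in that order). It uses 15 with an SD of 16, extrapolated from a series of 24 patients treated with EHA, to reach 18 per group and 44 in all. The Hypotheses section expects that "EHA provides a superior OES compared with ORIF by at least a difference of 15".

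The article gives no scale for the domain MCIDs or for the SD. It mentions no OES scale other than 12–60 and 0–48, and it describes no conversion.

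**The concern.** A target difference must be in the units of the outcome to which it is applied. Here the outcome is a sum of 12 items on 0–48, and the domain thresholds look too large to be parts of that sum: together they come to 46 of the 48 points. If they are on a different scale, a figure derived from them means nothing on 0–48 until it is converted.

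Two things are at stake. The first is the benchmark for clinical relevance. On 0–48, 15 points is 31% of the range and one and a half of the article's own 10-point grades. It is out of reach if the ORIF mean exceeds 48 − 15 = 33, which lies inside the good band. The second is the sample-size basis: whether 18 per group gives 80% power for the difference actually intended depends on whether the MCID and the SD share a scale.

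**Working it through.** **Inputs.** From Primary functional outcome: 12 items, five levels each, equal weight, total 0–48; domain MCIDs 19, 9 and 18; total-score MCID 15. From Sample size calculation OES: SD 16, power 0.80, printed alpha 0.005, 18 per group, 44 in all with 18% drop-out.

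**Step 1: the article's own sample size.** Normal approximation, n per group = 2(z₁₋α/₂ + z₀.₈₀)²(SD/Δ)², with Δ = 15 and SD = 16.

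- Two-sided alpha 0.05: 2 × (1.960 + 0.842)² × (16/15)² = 17.9, so 18 per group; 36/(1 − 0.18) = 43.9, so 44 in all. Both stated figures are reproduced. The t-based calculation gives 18.9, so 19.
- Two-sided alpha 0.005, as printed: 31 per group and 76 in all. This does not match.

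The printed alpha is a separate matter. Below, two-sided 0.05 is the main case because it reproduces the 18 per group, and 0.005 is shown beside it.

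**Step 2: can the domain MCIDs be points of the 0–48 total?** A five-level item spans at most 4 points, so the fewest items that can carry each difference are:

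- pain: 19/4 = 4.75, so 5 items
- function: 9/4 = 2.25, so 3 items
- social-psychological: 18/4 = 4.5, so 5 items

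The sum is 13 items, and the OES has 12. This holds for any split of the items over the three domains. It also holds for the raw 12–60 score, which has the same 4 points per item. The domain MCIDs are therefore on some other scale.

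**Step 3: where 15 comes from.** (19 + 9 + 18)/3 = 15.33, which rounds to 15. The article does not say that it averaged, but it derives 15 from these three values and offers no other route.

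**Step 4: size of the mismatch if the domain MCIDs are on 0–100 (assumption; not in the article).**

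- 15 × 48/100 = 7.2 points on 0–48; unrounded, 15.33 × 0.48 = 7.36.
- Overstatement of the target: 15/7.2 = 2.08, or 15/7.36 = 2.04.

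**Step 5: effect on sample size, under the same assumption, by the scale of the SD.**

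- *SD 16 also on 0–100.* On 0–48 it becomes 16 × 0.48 = 7.68. The ratio 7.2/7.68 equals 15/16, so 18 per group and 44 in all stand. Only the outcome scale and the threshold are wrong.
- *SD 16 on 0–48.* The standardised difference is 7.2/16 = 0.45. Two-sample t-test power:

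| Two-sided alpha | 18 per group | 22 per group | n per group for 80% power |
|---|---|---|---|
| 0.05 | 26% | 31% | about 79 |
| 0.005 (printed) | 6% | 8% | about 134 |

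With 7.36 in place of 7.2, at alpha 0.05, the powers are 27% and 32%.

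**The case against.** The strongest reply is that the factor of two comes from outside the article. Nothing in it puts the domains on 0–100, and the sources of the MCIDs and the SD are not available here. That stands: the mismatch is shown by the text, its size is not.

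Four stronger readings are tempting and are not supported.

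- A reader might infer that SD 16 must also be a 0–100 figure because it is large for a 48-point scale. The largest possible SD at mean m is √(m(48 − m)), which is √(40 × 8) = 17.9 at a mean of 40. An SD of 16 is possible there, and the article does not give the source mean. Both cases must stay open.
- A reader might infer that the trial will be declared a failure below 15 points. The Data analysis section plans an ordinary t-test or Mann-Whitney test with no margin. A significant difference of 8 points would still be significant; only its description as clinically relevant is affected.
- A reader might infer that about 7 points on 0–48 would satisfy the cited domain thresholds. An evenly spread 7.2-point gain is 15 on 0–100 in each domain, short of 19 for pain and 18 for the social-psychological domain.
- A reader might infer that the trial is underpowered. This follows only if the MCIDs are on 0–100 and the SD is on 0–48. If the two share a scale, the ratio of 15 to 16 is coherent.

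None of this rescues 15 as an MCID on 0–48. Nor is it a detail left to an analysis plan: the scale, the derivation and the threshold are all stated in the article, and they do not fit together.

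**Conclusion.** The concern holds. From the article's own scoring, the domain MCIDs cannot be in points of the 0–48 total, and the 15 derived from them has no valid basis on that scale. It nevertheless serves as total-score MCID, sample-size target and hypothesised difference. What suffers is the interpretation of clinical relevance and the justification of the sample size, not the validity of the planned significance test.

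The size is conditional. If the domain MCIDs are on 0–100, the stated target is about twice the intended one. The effect on power then ranges from none to a fall to roughly a quarter to a third at two-sided alpha 0.05, depending only on the scale of the SD.

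**What to change.** Before the 2-year analysis, check in the two cited sources the scale of the domain MCIDs and of the SD. Then put the analysed OES, the MCID and the SD on one stated scale, and change Primary functional outcome, Sample size calculation OES and Hypotheses together. There are two options:

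- analyse the OES on the scale of the MCIDs (for example 0–100, if that is what the source uses) and keep 15, with the SD on that scale; or
- keep 0–48 and restate the converted MCID (about 7 if the source is 0–100) and the SD on 0–48 (7.7 if its source is also 0–100).

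In either case, say openly how the total-score MCID was formed from the domain values, since taking a mean of domain MCIDs is itself a choice. Keep 44 patients; if the ratio of MCID to SD changes, restate the power and the alpha at which it is calculated.

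The cost is a check of two source figures and edits to three sections, with no extra patients. The downside is that the stated power may become less favourable. Doing this before results are seen matters, because a scale or threshold chosen afterwards would weaken any claim of clinical relevance.

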#### Secondary functional outcomes

##### Mayo Elbow Performance Score

Mayo Elbow Performance Score (MEPS) is a surgeon-administrated instrument that evaluates the outcome after elbow surgery [18]. There are four domains, including pain (0–45 points), range of motion (0–20 points), stability (0–10 points), and difficulties in daily activities (0–25 points) [3, 4]. The outcome can be interpreted based on a 100-point scale: 0–60, poor; 60–74, fair; 75–89, good; and 90–100, excellent [18]. The MCID has been defined as 10 [4].

##### Pain severity score

Pain is answered on a visual analogue scale (VAS) ranging from 0 to 10 (on a 100-mm scale), with 10 being the worst and 0 representing a pain-free elbow [15]. The MCID has been defined as 20 mm (two points) [28].

##### Range of motion

Range of motion (ROM) will be measured in degrees, both flexion/extension arc and supination/pronation arc. To our knowledge, the MCID of ROM in patients with distal humeral fractures has never been reported.

##### Patient satisfaction

Patient satisfaction of the treatment will be recorded using a five-item score (5, very satisfied; 4, satisfied; 3, neither satisfied nor dissatisfied; 2, dissatisfied; and 1, very dissatisfied).

#### Radiographic evaluation

Radiographic evaluation will be performed using anteroposterior and lateral radiographs. There is no specific and validated method to evaluate x-ray images after EHA/ORIF or to evaluate post-traumatic osteoarthritis of the elbow joint, so decreased height of the humeral, ulnar, and radial cartilage, bone healing and joint alignment, arthroplasty/plates loosening, and the presence of heterotopic ossification will be analyzed as binary outcomes (yes or no) by the primary investigator.

#### Complications and reoperations

We will record all complications related to the surgical procedure (nerve injuries, deep and superficial infections, malpositioning of the components, and instability) and reoperations (defined as any surgical intervention to the index elbow after the primary procedure).

Length of sick leave will be recorded.

### Follow-up

All patients will be followed actively for 10 years. To ensure the implant position, all patients will undergo a plain x-ray in two planes before discharge, which will usually be done on the first postoperative day. Then all patients will be followed actively with plain radiographs, clinical outcome, and patient-reported outcome at 3 months postoperatively and at 1, 2, 5, and 10 years.

### Protocol violations, patient drop-out, and revision

The number of patients who receive the allocated treatment will be reported. If ORIF is technically impossible, the surgeon remains free to use an EHA if it is believed to be in the best interest of the patient. A main analysis will be conducted on an intention-to-treat basis where all outcome scores from each patient are analyzed according to the randomization, irrespective of type of surgery received. If operative crossover does occur, a secondary analysis will be conducted on a per protocol basis. This analysis will only include patients who undergo surgery according to the randomization.

Patients who drop out of the trial will be recorded, and the reason for the drop-out will be noted. The patient will be included in the analysis with the latest follow up (last observation carried forward). Drop-outs before the 3-month evaluation cannot be included in the analysis due to lack of preoperative data. The number of patients who do not comply with rehabilitation will be recorded.

If a reoperation is needed, the reason and the operation type are recorded. If possible, the patient is evaluated using clinical outcome and patient-reported outcome prior to the revision procedure. The patient will remain in the study and they are included in the analysis with their latest follow-up.

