**Discussion:**

The main objective of this study is to investigate the best treatment option for AO/OTA type 13 C2 and C3 fractures of distal humerus in patients aged 50 years or above. We hypothesize that EHA results in fewer complications and superior functional outcome compared with ORIF and that the mechanical complications related to the linked articulation of TEA can be avoided.

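### Last observation carried forward lets 3-month or 1-year OES scores stand in for the 2-year primary outcome and can bias the comparison in either direction

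*Protocol article*

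**What the plan says.** The primary endpoint is fixed in the section on the primary functional outcome: "The Oxford Elbow Score (OES) will be used to assess the primary outcome at 2 years". The Follow-up section schedules "patient-reported outcome at 3 months postoperatively and at 1, 2, 5, and 10 years", so the only OES values that exist before the primary time point are those at 3 months and 1 year.

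The section on protocol violations, drop-out and revision sets the rule for patients who leave: "The patient will be included in the analysis with the latest follow up (last observation carried forward". It then adds: "Drop-outs before the 3-month evaluation cannot be included in the analysis due to lack of preoperative data". For reoperated patients it says: "The patient will remain in the study and they are included in the analysis with their latest follow-up". The same section calls the main analysis intention-to-treat.

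The Data analysis section plans a two-group t-test or Mann-Whitney test on outcome scores, with no model across visits. The per-protocol analysis addresses crossover only. No other missing-data method or sensitivity analysis is described.

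**The concern.** Carrying a score forward assumes that nothing changes between the last visit and 2 years. That is hard to defend here. The rehabilitation section says: "Full weight-bearing exercises are allowed after 3 months". The 3-month OES is therefore taken when full loading is only just beginning, and further improvement should be expected.

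The error cancels between arms only if the share carried forward times the recovery still to come is the same in both. The protocol gives no ground for presuming this, since it expects the arms to differ: "We hypothesize that EHA results in fewer complications and superior functional outcome compared with ORIF". A joint replacement and a healing fracture may also recover at different rates, even though both arms follow the same rehabilitation programme.

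The two-group test also counts each carried value as an observed 2-year score. In a trial of 44 patients that plans for 18% drop-out, a few such values can move the primary estimate and its interval.

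**Working it through.** **Inputs from the protocol.** Difference 15 and SD 16 ("Sample size calculation was performed with a standard deviation (SD) of 16, a MCID of 15"), power 0.80, 18 per group, 18% drop-out, 44 in total, 1:1 allocation.

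**The plan's own figures.** 2 × 18 / (1 − 0.18) = 43.9, so 44, which agrees. 18% of 44 is 7.9, about 8 patients. The 18 per group reproduces at two-sided alpha 0.05: 2 × (1.960 + 0.842)² × 16² / 15² = 17.9, so 18. The printed alpha of 0.005 gives 31 per group. That mismatch is a separate matter; the simulation below uses 0.05 because it matches the stated sample size.

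**Bias formula.** For each arm let p be the share of analysed patients whose score is carried forward, and g the mean OES recovery those patients would still have made by 2 years. The expected mean under LOCF is the true 2-year mean minus p × g. Hence

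bias in (EHA − ORIF) = p_ORIF × g_ORIF − p_EHA × g_EHA.

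The protocol gives neither p by arm nor g. The values below are assumptions, with g on the same scale as the 15-point target.

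| p EHA | p ORIF | g EHA | g ORIF | Calculation | Bias | Share of 15 |
|---|---|---|---|---|---|---|
| 18% | 18% | 10 | 10 | 1.8 − 1.8 | 0 | 0% |
| 18% | 18% | 5 | 15 | 2.7 − 0.9 | +1.8 | 12% |
| 10% | 26% | 10 | 10 | 2.6 − 1.0 | +1.6 | 11% |
| 26% | 10% | 10 | 10 | 1.0 − 2.6 | −1.6 | 11% |
| 10% | 26% | 5 | 15 | 3.9 − 0.5 | +3.4 | 23% |
| 26% | 10% | 15 | 5 | 0.5 − 3.9 | −3.4 | 23% |

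**Timing of drop-out.** Patients lost before 3 months are excluded, not carried, and those lost after 1 year have less recovery left. As an illustration, split the 18% equally over the three intervals. Each carried group is then 6/94 = 6.4% of those analysed. Take g of 15 (ORIF) and 5 (EHA) for 3-month scores and one third of that for 1-year scores. The bias is 0.064 × 10 + 0.064 × 3.33 = 0.85, against 1.8 in the second row.

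**Standard error.** With SD 16 and 22 per arm, the standard error is 16 × √(2/22) = 4.82. With the 18 per arm who would have an observed 2-year score, it is 16 × √(2/18) = 5.33. LOCF reports something close to the former.

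**Simulation.** 22 per arm, SD 16, assumed correlation 0.6 between carried and 2-year scores, drop-out unrelated to outcome, two-sided 0.05 t-test, 8,000 runs, true difference 0:

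| p EHA / ORIF | g EHA / ORIF | SE, LOCF | SE, observed only | Coverage, LOCF | Type I error, LOCF |
|---|---|---|---|---|---|
| 18% / 18% | 0 / 0 | 4.79 | 5.31 | 95.2% | 4.8% |
| 18% / 18% | 10 / 10 | 4.93 | 5.32 | 94.7% | 5.3% |
| 18% / 18% | 5 / 15 | 4.96 | 5.30 | 93.4% | 6.6% |
| 10% / 26% | 10 / 10 | 4.93 | 5.35 | 94.2% | 5.8% |
| 26% / 10% | 10 / 10 | 4.92 | 5.33 | 93.5% | 6.5% |
| 10% / 26% | 5 / 15 | 5.01 | 5.34 | 90.2% | 9.8% |

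The LOCF standard error is 6% to 10% smaller than that from observed 2-year scores. Coverage is nominal in the two symmetric rows and falls to 90% to 94% in the others.

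**The case against.** The other side has several fair points.

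- **Drop-out may be low.** The Discussion plans telephone calls and home visits for patients who miss follow-up, and 18% is an allowance rather than a forecast. About 8 wrong-time scores is a ceiling. This stands and may reduce the problem, but it does not repair the rule for those still lost.
- **Direction is unknown.** A reader might infer that LOCF favours EHA, the hypothesised winner. The documents do not support that: they give no recovery curves or drop-out by arm, and the same formula gives −1.6 or −3.4 when the inputs are reversed.
- **The standard error is not always invalid.** A reader might infer that LOCF always understates uncertainty. With equal drop-out and no remaining recovery, the LOCF standard error matched the estimator's actual spread (4.79 against 4.78) and coverage was nominal. What stands is narrower: it is smaller than the 2-year data actually observed support, and coverage suffers when the arms differ.
- **The bias could be set against a smaller target.** Reading the 15 as about 7 points on the 0–48 scale would turn 3.4 points into nearly half the target. The protocol does not put the 15 on another scale, and if the target is rescaled the recovery must be too: 3.4 × 0.48 = 1.63, and 1.63 / 7.2 is again 23%.
- **A better model does not complete the intention-to-treat set.** Patients with no OES contribute nothing to a repeated-measures model either. The exclusion of early drop-outs is therefore not cured by dropping LOCF, and imputing them from allocation, age and sex adds little information.

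An unseen analysis plan is no answer, because the article states the rule rather than leaving it open.

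**Conclusion.** The point holds in conditional form. LOCF is the only stated handling of drop-outs for the 2-year OES, and it puts scores taken during recovery in place of the endpoint. The bias is zero only when share carried times remaining recovery is equal in the two arms. Under the assumed ranges it lies between −3.4 and +3.4 points, at most about 23% of the 15-point target, and is smaller once early exclusions and late drop-outs are allowed for. In the most unequal scenario simulated, type I error rises from 5% to about 9.8% and coverage falls to about 90%. These sizes rest on assumed drop-out shares, recovery and correlation, none of which the protocol gives.

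One point is unresolved. The reoperation sentence does not say whether a score taken before revision may stand as the 2-year value. A reader might infer that it does, but the text does not settle it. If it does, the same problem reaches reoperated patients who never dropped out.

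**What to change.** Replace LOCF as the primary handling by a likelihood-based repeated-measures model on the OES at 3 months, 1 year and 2 years, with treatment, visit, treatment-by-visit, age stratum and sex, and an unstructured covariance. Take the 2-year treatment contrast as the primary result. Early scores then inform the 2-year estimate instead of replacing it. Amend both the drop-out section and the Data analysis section.

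Keep LOCF at most as a sensitivity analysis. The model assumes data missing at random, so add a sensitivity analysis for departures from that assumption. Report by arm the number of patients with no OES, and include them by multiple imputation from allocation, age and sex in a further sensitivity analysis. State which score is used for reoperated patients.

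The visits are already scheduled, so no new data are needed, and a three-visit unstructured covariance has only six parameters. The costs are slightly more analysis work, a model for a bounded score in place of the simple t-test or Mann-Whitney option, and a possibly somewhat wider confidence interval. The change should be made before the 2-year analysis.

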## Discussion

We will attempt to avoid the type-II error (when the hypothesis testing does not reject the null hypothesis, even though the null should have been rejected) by using a proper sample size and by adding 18% to sample size compensating for drop-outs. The drop-out bias will be minimized by obtaining permission to call patients who do not show up for subsequent follow-up and also to visit the patients at home. Selection bias will be avoided through randomization. If ORIF during the surgery is regarded to be technically impossible, the procedure can be converted to EHA. In order to follow the principle of the intention-to-treat, the patient will continue to be in the ORIF group and included in the analysis according to the randomization. A secondary analysis will be conducted on a per protocol basis where only patients who undergo surgery according to the randomization are included.

The consequences of having unblinded patients are unknown. It may introduce bias to the study, which, in most cases, will be in favor of the intervention. In the present study, the intervention and the comparator are surgery and the patients and blinding of the patients may not be as important as in studies where surgery is compared with non-surgery. The primary outcome is a patient-administered questionnaire and does not involve any persons affiliated with the study. It was chosen as the primary outcome to avoid observer bias. The secondary outcomes are not observer blinded and the results will be interpreted carefully due to the risk of bias.

The trial will provide high-quality evidence regarding the short- and long-term clinical and patient-reported outcomes of ORIF and EHA. We use the same outcome scores as in previous randomized trials comparing TEA and ORIF [8, 9, 17]. This makes it possible not only to compare the results but also to include the results in future systematic reviews and meta-analyses. We believe that the results from the present trial, together with results from other randomized trials, can be used to establish a treatment algorithm for distal, intraarticular humerus fractures.

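### The main analysis is labelled intention-to-treat, but patients lost before 3 months are left out, so the analysed set is a modified intention-to-treat set

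*Protocol article*

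**What the plan says.** Three statements in the protocol article's section on protocol violations, patient drop-out and revision bear on the analysis set.

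- The label: "A main analysis will be conducted on an intention-to-treat basis where all outcome scores from each patient are analyzed according to the randomization".
- The rule for drop-outs: a patient who leaves is analysed with the last available score carried forward. For those who leave early, "Drop-outs before the 3-month evaluation cannot be included in the analysis due to lack of preoperative data".
- The rule for reoperated patients: "The patient will remain in the study and they are included in the analysis with their latest follow-up".

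The section also provides that "Patients who drop out of the trial will be recorded, and the reason for the drop-out will be noted".

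Other sections complete the picture. The preoperative data listed are sex, age and imaging, with no outcome score. The first outcome score is taken at 3 months (Follow-up). The primary outcome is the OES at 2 years. The Data analysis section compares scores between the two groups by t-test or Mann-Whitney test and states no baseline term.

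**The concern.** An intention-to-treat analysis is normally understood to cover every randomised patient. Here a fixed rule removes some of them because of something that happens after randomisation, and the label stays the same. A reader of the results would take the set for something it is not.

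The label matters because loss in this window need not be random. Patients and surgeons know the allocation, and randomisation takes place just before surgery, so the first 3 months cover the operation and early recovery. A patient who does badly, or is unhappy with the treatment received, and leaves in that period contributes nothing to the OES or the other scores. If this happens more in one arm, that arm's mean score looks better than it should.

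The reason given also makes the exclusion sound unavoidable, which it is not.

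**Working it through.** **Step 1. Is the exclusion forced by the missing preoperative score?**

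- The planned test compares 2-year scores between arms. Neither a t-test nor a Mann-Whitney test uses a preoperative value.
- Last observation carried forward needs an earlier score. The first one is taken at 3 months, so a patient lost before then has nothing to carry forward.
- Arm, age group and sex are known for every randomised patient, because arm is the allocation and the other two are the stratification factors.

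The exclusion therefore follows from the chosen missing-data method, not from the comparison itself.

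**Step 2. How many patients could be involved?**

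Inputs from the sample size section: 18 per group, 18% drop-out allowance, 44 in all.

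- The plan's total reproduces: 2 × 18 = 36, and 36 / (1 − 0.18) = 43.9, rounded up to 44, or 22 per arm.
- Allowance: 44 − 36 = 8 patients, or 4 per arm if evenly split.
- The share lost before 3 months is not given. The analysed set lies between 44 (no early loss) and 36 (the whole allowance lost early).

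The 18 per group is taken as given; its derivation does not bear on this point.

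**Step 3. How far could an arm's mean move?**

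Let k of 22 patients in one arm be left out, and let their mean 2-year OES lie d points below the mean m of the retained patients. Then

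full-arm mean = [(22 − k) × m + k × (m − d)] / 22 = m − k × d / 22,

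so the retained-patient mean overstates the full-arm mean by k × d / 22. Both k and d are assumptions, and no offsetting loss in the other arm is assumed.

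| k | d = 15 | d = 20 |
|---|---|---|
| 1 | 0.68 | 0.91 |
| 2 | 1.36 | 1.82 |
| 3 | 2.05 | 2.73 |
| 4 | 2.73 | 3.64 |

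With d between 10 and 30, the range for k = 1 to 4 widens to 0.45 to 5.45.

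The reference point matters. If d is measured from the full-arm mean instead, the overstatement is k × d / (22 − k). For d = 20 that is 20/21 = 0.95 at k = 1 and 80/18 = 4.4 at k = 4. The table uses the retained patients as reference.

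**Step 4. Scale.**

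- Against the 15-point target: 3.64 / 15 = 24% at the top of the table and 0.68 / 15 = 5% at the bottom.
- Against sampling error, with the plan's SD of 16 and 18 per arm: standard error of the difference = 16 × √(2/18) = 5.3 points. One or two early losses at d = 20 (0.91 or 1.82 points) are 0.17 or 0.34 of one standard error; four are 3.64 / 5.33 = 0.68.

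**The case against.** The strongest reply is that the protocol says what it means by the term: "all outcome scores from each patient are analyzed according to the randomization, irrespective of type of surgery received". On that reading, intention-to-treat deals with crossover. A patient without a score has none to analyse, no existing score is discarded, and the exclusion is stated openly with its reason. The Discussion's phrase "In order to follow the principle of the intention-to-treat" likewise concerns only conversion from fixation to hemiarthroplasty. This stands in part: crossovers are handled correctly, and the Discussion is no evidence of a second contradiction. It does not rescue the label, because readers will take it to mean all randomised patients.

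A reader might infer that the plan hides early failures altogether. The documents do not support that. Complications and reoperations are recorded in their own right, partly through the hospital record and a national register. Reoperated patients stay in the study, and "If possible, the patient is evaluated using clinical outcome and patient-reported outcome prior to the revision procedure". Drop-outs and their reasons are recorded, and telephone calls and home visits are planned to limit loss. The concern is confined to the score analyses.

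A reader might also infer that the primary result will be biased towards a particular arm. No early-loss rate is given, overall or by arm, so neither direction nor size can be derived. The upper figure requires one arm to lose its full share of the allowance within the first 3 of 24 months, with a deficit larger than the trial's own target difference.

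Two further points stand. Imputation from arm, age group and sex alone largely reproduces the available-case result, so it would not by itself address non-random loss. And the absence of a sensitivity analysis from a protocol article is no fault, since that may be left to an analysis plan. What can be faulted is the label together with the stated exclusion and its reason.

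**Conclusion.** The point holds in a limited form. The protocol fixes a modified intention-to-treat set and calls it intention-to-treat, on grounds that follow only from last observation carried forward. Because this is stated outright, it is not a detail left to an unseen analysis plan.

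The consequence is a possible bias in the score analyses of unknown size and direction. The 0.7 to 3.6 points worked out above are an illustration. They rest on assumed numbers of early losses (1 to 4 of 22, in one arm only) and an assumed deficit (15 to 20 points below the retained patients). One or two losses would matter little beside the sampling error; four with a large deficit would amount to about a quarter of the target difference. The correction should be made, but the point does not undermine the design.

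**What to change.** 1. Rename the main analysis set: modified intention-to-treat, meaning randomised patients with at least one OES, analysed in their randomised arm. State that the exclusion of earlier drop-outs arises from the missing-data method.
2. Report the number of drop-outs before 3 months, with reasons, by arm. The reasons are already to be recorded; only the split by arm is new.
3. Add one sensitivity analysis of all 44 randomised patients. Impute missing scores by arm, age group and sex, then shift the imputed values downward, separately by arm, until the conclusion changes (tipping point). The shift must carry this analysis, since the imputation alone adds little. Report deaths separately, because a 2-year OES for a patient who has died is hypothetical.

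The cost is a change of wording and one extra analysis. The interval from that analysis may be slightly wider. No treatment, visit or sample size changes.
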